#### Qualitative Data Analysis Plan

Interviews will be video recorded, and all data will be transcribed verbatim. Data in Bahasa Indonesia will be translated into English for co-investigators who are only proficient in English. Qualitative data will be analyzed to identify a thematic framework [19], guided by a theoretical model of a PBD for controlling hypertension in farmers [20]. The emerging codes will be analyzed thematically according to the framework if they are coherent. The team members will repeatedly read each document and transcript to familiarize themselves with the whole data set and ensure the accuracy of the transcription reviews. Codes will be applied to raw data and then grouped into clusters to generate themes. Consensus on the codes and themes must be reached among at least three of the investigators (TS, HR, FK, IR, and [name]). The data will be compared in an ongoing manner to identify the true meaning of the data. Member checking and investigator reflexivity will be used to increase the credibility and reliability of the data. Data credibility will be enhanced through further analysis of interview and field notes, and views from the different categories of farmers having different sociodemographic backgrounds (eg, those with different grades of hypertension), as well as through triangulation involving multiple investigators. The content of the interviews will be shared with some participants, and their feedback on the findings will be sought for validation purposes (respondent validation). Investigators involved in the data analysis will collect and explain their biases or assumptions during data analysis and interpretation (reflexivity). Raw data, interpretations, and conclusions will be discussed with peers (peer debriefing). Confirmability will be enhanced by keeping an audit trail of the audio/video files, electronic documents, original field notes, and translations [21].

### Phase II: Quantitative Phase

#### Activity 1: Questionnaire Development and Validation

##### Overview

In activity 1, we will develop a questionnaire of an acceptable PBD for controlling hypertension, according to the qualitative data in phase I. The quotations from raw data will become questionnaire items, themes will become scales, and codes will become variables. A Likert score will be used for measurement (range of 1 to 4 points), which will determine the levels of expectations and acceptability. Based on the scores of the items or the summed scores, expectations and acceptability can be categorized into the following 3 categories: affordable, accessible, and achievable. Categorization will be performed using a statistical formula. If the data are normally distributed, the grade level will be based on the mean value; otherwise, the median will be used (X < mean/median – 1 SD; mean/median – 1 SD < X < mean/median + 1 SD; mean/median + 1 SD < X).

The questionnaire will have the following 2 sections: (1) sociodemographic characteristics of hypertension and (2) acceptable PBD for controlling hypertension. The instructions and descriptions of the definition, concept, and criteria of a PBD will be provided at the beginning of the questionnaire. The Pender Health Promotion Model will guide the questionnaire’s qualitative analysis and item design. After performing a member check and assessing face and content validity with an expert committee, we expect the final version of the questionnaire. The expert committee will include investigators with expertise in qualitative research (HR), statistical analysis (FK), public health (TS), and research methodology ([name] and IR).

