##### Measures

To meet the study objectives, the questionnaire will consist of the following sections: (1) sociodemographic characteristics and (2) the level of acceptability of a PBD to treat hypertension among farmers. The sociodemographic characteristics will include age, gender, marital status, education (no formal education, elementary school, middle school, and high school or higher), household monthly income per capita (less than US $65.82, US $65.82-131.65, US $131.66-197.47, and over US $197.47), duration of hypertension (years), grade of hypertension based on the JNC VIII criteria, and living condition (with children or a spouse). In section 2 of the questionnaire, a 4-point Likert scale will be used to assess the level of acceptability of a PBD to treat hypertension among farmers. Expectations will be measured as follows: 1, strongly disagree; 2, disagree; 3, agree; and 4, strongly agree. A higher score will indicate a higher level of acceptability of a PBD to treat hypertension among farmers. The association of sociodemographic factors with the different categories of expectations and acceptability will be determined through statistical analysis.

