##### Analysis Plan

The data from the questionnaire will be inputted into SPSS (IBM Corp) for analysis. We will perform data cleaning to check each data point from the questionnaire and ensure there are no missing data from the entire questionnaire. We will only use completed questionnaires for analysis. After the data cleaning process is complete, we will perform the data analysis process.

We will use descriptive statistics to describe the characteristics of the respondents and the level of acceptability of a PBD to treat hypertension among farmers according to data distribution. Numerical variables will be shown as means and standard deviations or medians and interquartile ranges, while categorical variables will be shown as absolute frequencies and percentages. We will use the chi-square test to examine the sociodemographic factors associated with farmers’ different categories of acceptability. With the 95% CI, a *P* value of <.05 will be considered statistically significant.

We will use multiple logistic regression models to estimate the associated and independent factors from the sociodemographic factors and the level of acceptability of a PBD among farmers. In the case of a low event rate and low sample size for expectations and acceptability in the definite form, we may recode them into tertiles and use the lowest score category as the reference group. Alternatively, we may conduct multiple linear regression analyses with the 2 dependent variables as continuous variables. We will also include any independent factors with a *P* value <.20 from the univariable regression analysis in the multiple regression analysis. Multicollinearity between independent variables will be checked according to a tolerance value <0.4 (variance inflation factor ≥2.5). In the presence of multicollinearity, we will select the more critical or essential variables from clinical perspectives for use in the final regression analysis. We will check all models, check Q-Q plots for normality, check residual plots for linearity, and check homogeneity assumptions, as well as assess model fitting.

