A PBD model will provide farmers with an alternative solution that has independent, safe, and comfortable features for their needs. It could also be used to adapt and transform existing hypertension programs for farmers and their family members. With a better understanding of farmers’ expectations and acceptability of a PBD model in public health, researchers, stakeholders, and policymakers may be able to effectively develop a complete model that incorporates appropriate technologies and integrates relevant medical services, and yet remains affordable to benefit the majority of farmers. This would facilitate the transformation of traditional hypertension interventions to smart and local interventions, which include necessary skill sets or required training for PHNs and other health care professionals to meet expectations.

The findings of this study will be presented at conferences and published in peer-reviewed journals. We will publish the results of this research in academic journals. We will also present this research at national and international conferences. The data from this study will be presented in a research report to the Ministry of Cultural Education, Research and Technology, and Higher Education on the BIMA system dashboard (BIMA – Kemdikbudristek) as restricted data. In addition, research data will be reported to the Institute for Research and Community Service, University of Jember (organizer in research activities). Furthermore, the research results of the first year and second year will be presented in a manuscript. The manuscript will be submitted to a reputable international journal in the areas of hypertension and NCD management.

Disseminating our study findings will significantly contribute to the advancement of science and holistic nursing services for farmers with hypertension in the community.

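### The survey names three ordered score bands affordable, accessible and achievable, so a label shows only a farmer's score level, not a judgement on any of these properties

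*Protocol article*

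**What the plan says.** All references are to the Protocol article.

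- **Phase II, Activity 1, Overview (scoring).** "A Likert score will be used for measurement (range of 1 to 4 points), which will determine the levels of expectations and acceptability". Either item scores or their sum may be used.
- **Same section (categories and rule).** On that basis, "expectations and acceptability can be categorized into the following 3 categories: affordable, accessible, and achievable. Categorization will be performed using a statistical formula". The centre is the mean if the data are normal and the median otherwise, and the bands are "X < mean/median – 1 SD; mean/median – 1 SD < X < mean/median + 1 SD; mean/median + 1 SD < X".
- **Activity 2, Measures (direction).** "A higher score will indicate a higher level of acceptability of a PBD to treat hypertension among farmers". This section also plans to relate sociodemographic factors to the categories of expectations and of acceptability.
- **Activity 2, Analysis Plan (use).** "We will use the chi-square test to examine the sociodemographic factors associated with farmers’ different categories of acceptability". Logistic regression follows, with tertiles or continuous scores as fallbacks.
- **Discussion, Contributions of the Study.** Understanding farmers' expectations and acceptability is hoped to help build a model that "incorporates appropriate technologies and integrates relevant medical services, and yet remains affordable to benefit the majority of farmers".

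No section ties a label to items on affordability, access or achievability, and none says which label belongs to which band.

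**The concern.** Three names are given, then a formula that yields exactly three bands, and the formula is presented as the way to sort respondents into the named categories. The bands are ordered and exclusive: each farmer falls in one of them for expectations and one for acceptability. The names are neither ordered nor exclusive.

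Objective 2 includes the level of acceptability and its associated factors. If the labels were carried into the results, the survey would report the percentage of farmers in an affordable, an accessible and an achievable group, and the factors associated with belonging to each. A reader would take these as findings on cost, access and feasibility, when they would be findings on low, middling and high scores. The Discussion shows that affordability matters to the authors, though it does not say that the questionnaire category will be used to judge it.

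**Working it through.** The plan gives no figure to reproduce here. The check is of the rule itself.

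**1. The rule as a function.** Let X be a respondent's score, c the sample mean or median and s the sample SD.

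- label = first name used if X < c − s
- label = second name used if c − s < X < c + s
- label = third name used if X > c + s

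The only input is the position of X relative to the sample. This is so for every assignment of the three names to the three bands.

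**2. Share of farmers in each band.** For a normal score with c the mean, P(X < c − s) = Φ(−1) = 0.159, the middle share is Φ(1) − Φ(−1) = 0.683, and the upper share is 0.159. With the survey's 263 respondents (Activity 2, Sample Size Estimation):

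- lower band: 263 × 0.1587 = 41.7
- middle band: 263 × 0.6827 = 179.5
- upper band: 41.7

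These shares follow from the cut points. They would be the same in a population where the diet is cheap and in one where nobody can afford it.

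**3. Illustrative simulation.** All of the following are assumptions, because the items do not yet exist: 12 four-point items, 4 on each property; one common factor (SD 0.7) plus item noise (SD 0.8); thresholds at −1, 0 and 1; and three overall levels of agreement.

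| Agreement | Mean total (SD) | Share low / middle / high | Mean affordability item, low / middle / high band |
|---|---|---|---|
| Low | 22.1 (6.8) | 18.1% / 63.6% / 18.2% | 1.14 / 1.78 / 2.75 |
| Medium | 30.0 (7.7) | 18.4% / 63.1% / 18.5% | 1.57 / 2.50 / 3.43 |
| High | 37.9 (6.8) | 18.3% / 63.5% / 18.1% | 2.24 / 3.22 / 3.86 |

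The shares barely move although opinion of the diet changes greatly. On the protocol's scale 3 means agree. Suppose affordable named the top band, the most favourable pairing. Under low agreement its members would average 2.75, short of agreeing. Under high agreement the 63.5% in the middle band would average 3.22 and still not be called affordable. If affordable named the bottom band, it would go to the farmers who rate affordability lowest in all three scenarios.

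**4. Single respondents, medium scenario.** The cuts are 30.0 − 7.7 = 22.3 and 30.0 + 7.7 = 37.7.

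- Farmer A gives 4 to the four affordability items and 2 to the other eight: 16 + 16 = 32.
- Farmer B gives 1 to the four affordability items, 3 to the four access items and 4 to the four achievability items: 4 + 12 + 16 = 32.
- Farmer C gives 4 to everything: 48.
- Farmer D gives 1 to everything: 12.

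A and B hold opposite views on affordability and receive the same label. C endorses all three properties and receives one name. D rejects all three and still receives one of the three favourable names. No pairing of names with bands removes these results.

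**The case against.** The strongest reply is that the three words may be meant as domains, each graded low, middle and high. The section calls the output of the formula a grade level, plans to turn qualitative themes into scales, and allows scoring by item. The reading is possible, but the text does not say it: it gives three categories and a formula for sorting into them, whereas three domains with three grades would make nine cells. Item-level scoring does not help either, since an answer to one item would still be sorted into bands carrying all three names. If domains were intended, the correction needed is the same.

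A second reply is that the Analysis Plan never uses the three words. It speaks of categories of acceptability, may take the lowest-scoring tertile as reference, and may use continuous scores, so the tests are framed as comparisons of ordered levels. This stands in part. A misleading report is a risk of following the Activity 1 rule, not something the plan announces. But the Activity 1 categories are the only ones defined before the fallbacks, so the primary categorical analysis inherits them.

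Third, the questionnaire is still to be developed and will pass expert review and cognitive debriefing. That makes the correction easy, but does not make the stated rule sound.

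**Conclusion.** The point holds for the survey. The protocol fixes a categorisation whose names state something its bands cannot measure, under any pairing and any cut points on a single score. This conclusion follows from the text and needs no simulation. The band shares of 15.9%, 68.3% and 15.9% assume a normal score. The simulated values also rest on an assumed item count, split and correlation, and are not forecasts for this survey.

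Two stronger readings are not supported.

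- **Affordable is assigned to the farmers who accept the diet least.** A reader might infer this from the order of the two lists together with the stated direction of the score. It is the natural guess, but the protocol never makes the pairing, so any claim that results would be reversed is conditional on it.
- **The label is unrelated to what farmers answer about affordability.** Any affordability items would enter a summed score, and the simulation shows their mean rising from the bottom to the top band. The accurate statement is that such answers act only through the total and cannot be told apart from the rest.

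The trial's main outcomes, systolic and diastolic blood pressure, are unaffected.

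**What to change.** In Phase II, Activity 1, Overview, name the three bands low, moderate and high, separately for expectations and for acceptability. Use those names in the Measures and Analysis Plan sections of Activity 2.

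If affordability, accessibility and achievability are to be reported, score each as its own subscale from its own items, in line with the section's plan to derive scales from themes. Report each subscale's mean and the percentage agreeing, for example those with an item mean of at least 3. One farmer can then rate all three high or all three low.

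The cost is a change of wording, settled before the questionnaire is finalised, and three extra summaries. No participants or procedures are added. The one drawback is that each subscale has fewer items than the total and so is less reliable.

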##### Validation and Reliability

A cognitive debriefing involving 10 people to further assess the face and content validity of the questionnaire will be performed (5 expert nurses on hypertension and 5 nutritionists). Feedback will be discussed by the expert committee, and it will determine the appropriateness and completeness of the questionnaire and ethical considerations in the process. The next analysis step is the COSMIN (consensus-based standards for the selection of health measurement instruments) checklist developed in an international Delphi study to estimate the quality of selected measurement instruments. It measures internal consistency, reliability, measurement error, content validity (as well as face validity), structural validity, hypothesis testing, cross-cultural validity (the 3 aspects of construct validity), criterion validity, and responsiveness. Based on the checklist, items will be sorted by experts in the group to establish face, content, and construct validity in activity 1. The duration to finish the questionnaire is estimated to be less than 30 minutes. Further validation of the questionnaire will be conducted in activity 2. Cronbach alpha will be applied to prove the internal consistency (0.70 or higher is considered as good) of the expectations and acceptability questionnaire. Exploratory factor analysis using principal component analysis will be performed to examine the structural validity of the expectations and acceptability questionnaire separately.

In addition, the Kaiser-Mayer-Olkin test of sampling adequacy, the Bartlett test of sphericity, and the scree plot will be used to check the unidimensionality of the expectations and acceptability questionnaire. The convergence criteria will be set at an eigenvalue above 1. Construct validity (hypothesis testing) will be tested when comparing the responses to the expectations or acceptability of 1 item (yes or no). We hypothesize that the highest tertile expectation will be associated with willingness measured by a repeat measurement value of at least 2.0. The highest tertile acceptability will be related to willingness measured by a repeat measurement value of at least 3.0. It is also hypothesized that expectations and acceptability will correlate at a coefficient of at least 0.4. One-month intrarater test-retest reliability will be assessed in a random sample of at least 50 older people throughout the data collection period in activity 2.

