**Methods:**

We will use the exploratory sequential mixed methods approach. There will be a qualitative study (phase I) in 2022 and a quantitative study (phase II) in 2023. We will analyze data using a thematic framework in phase I. In phase II, the study will involve (1) questionnaire development and validation; (2) examination of the prevalence of hypertension, the level of acceptability of a PBD, and the associated factors; and (3) a randomized controlled trial. We will recruit farmers with hypertension who meet the study criteria. Moreover, in phase II, we will invite expert nurses and nutritionists to assess the face and content validity of the questionnaire. We will use multiple logistic regression models to estimate the associated sociodemographic factors and the level of acceptability of a PBD. Furthermore, a linear generalized estimating equation will be used to estimate the parameters of a generalized linear model with a possible unmeasured correlation between observations from different time points for systolic and diastolic blood pressure.

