## Introduction

Hypertension contributes to 12.8% of the total 7.5 million deaths worldwide [1]. The prevalence of hypertension in Indonesia is 33.4% [2], while in East Java province, it is 20.43% [3]. Farming communities have a high risk of health problems [4], including hypertension [5-7]. Hypertension among farmers in Indonesia has reached 36.1% [8]. Our previous study found that the incidence of hypertension among farmers in agricultural areas was 35.8% [9]. This shows the magnitude of the problem of hypertension among farmers, and there is a need for the management of care using an agricultural health nursing (agronursing) approach to realize the health status of farmers.

Agronursing can facilitate occupational health and safety among farmers [9]. Farmers’ health problems are generally caused by a lack of knowledge and skills in health management, which can lead to hypertension [10]. Most farmers with hypertension have a low level of education, so skills in self-care management are lacking [11]. Hypertension among farmers is also caused by an unhealthy lifestyle [9] and inadequate nutrition [12]. High consumption of unhealthy foods among farmers, such as high-sodium foods [6], and low knowledge about diet [13] can increase the risk of hypertension in farmers. Therefore, dietary management with a plant-based diet (PBD) needs to be introduced, and the basic principles of hypertension nursing care for farmers need to be developed.

Natural agricultural resources should be considered in the management of hypertension among farmers. The basic principles of hypertension care among farmers should be developed through optimizing the agricultural sector’s potential by consuming a PBD that prioritizes vegetables and fruits [14]. Therefore, it is necessary to formulate the basic concepts and principles of a PBD in nursing care management for farmers with hypertension based on the agronursing approach.

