##### Sampling Process

Representative research respondents will be selected by collecting available data on public health services. Farmers with hypertension are listed as regular patients in the Posbindu PTM (Pos Pembinaan Terpadu Penyakit Tidak Menular) program of the public health services. The data obtained will be assessed in a random process to select respondents using a simple random sampling technique. We will use a randomizer application that is available online to select respondents. Respondents selected from the randomizer application will then be included in the list of research respondents. We will follow the activities of the Posbindu PTM program as well as meet with research respondents who have been selected to be able to collect research data. We will print out the questionnaire and give it to the research respondents to fill out. Our team will assist farmers in filling out questionnaires to ensure that the questionnaires given are filled out completely and accurately.

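### All ten cognitive-debriefing places go to health professionals, so the step cannot observe whether farmers understand the drafted items and the 4-point scale

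*Protocol article*

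**What the plan says.** Validation and Reliability (Activity 1) states: "A cognitive debriefing involving 10 people to further assess the face and content validity of the questionnaire will be performed". The bracket that follows names the whole panel: "performed (5 expert nurses on hypertension and 5 nutritionists". The abstract's Methods paragraph agrees: "we will invite expert nurses and nutritionists to assess the face and content validity of the questionnaire". The results go to investigators: "Feedback will be discussed by the expert committee".

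The people who will answer the questionnaire are different. The Introduction says: "Most farmers with hypertension have a low level of education". The survey's Measures section lists the education categories as "no formal education, elementary school, middle school, and high school or higher". The survey's Sampling Process section adds: "Our team will assist farmers in filling out questionnaires".

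Other parts of the article also bear on comprehension. The Activity 1 overview derives items from interview quotations, puts a definition of the plant-based diet at the start of the form, and mentions a member check before the final version. Validation and Reliability defers further validation to activity 2. That validation consists of Cronbach alpha, exploratory factor analysis, comparison with a yes/no item, an expected correlation of at least 0.4 between expectations and acceptability, and a one-month test-retest in at least 50 people.

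**The concern.** Cognitive debriefing is meant to find out how intended respondents read an item and choose a response. Nurses and nutritionists can say whether an item is relevant and whether a topic is missing. They cannot stand in for a farmer with little or no schooling who has to follow a written definition and then choose among four grades of agreement.

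If items are misread, the acceptability level reported under objective 2 is measured with error of unknown direction. Education is one of the sociodemographic factors to be related to acceptability. If misreading, or reliance on staff help, is more common among the less educated, an apparent association with education could partly be an artefact of comprehension, and the regression cannot separate the two. The Activity 3 overview also names acceptability as a trial outcome, so the same instrument weakness would carry over to it.

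**Working it through.** **Panel count (Validation and Reliability).** 5 expert nurses + 5 nutritionists = 10, which reproduces the stated total. Places left for farmers: 10 − 10 = 0. The composition is stated outright, so it is not a detail lost in condensing the protocol.

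**Is the drafted questionnaire tested on farmers anywhere else before activity 2?**

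| Step | Section | What it covers |
|---|---|---|
| Pilot test | Phase I, Data Collection | The interview guides |
| Respondent validation | Qualitative Data Analysis Plan | Interview content and findings |
| Items from quotations | Activity 1, Overview | The source of the wording; no test of the drafted items |
| Definition on the form | Activity 1, Overview | An aid to the reader; no test of understanding |
| Member check | Activity 1, Overview | Participants and task not stated |
| Farmers and families used in planning | Study Overview | A general statement; no item-testing role given |
| Staff help with completion | Activity 2, Sampling Process | Given while the survey is running |

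No row describes an item-comprehension test in farmers. The member check comes closest, but its content is not stated.

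**Would the checks in activity 2 find the problem?** Random or item-specific misreading could show as weak loadings or poor retest agreement, and the yes/no comparison might flag some of it. Misreading that is consistent across items and occasions, or a habit of agreeing, could still give a high alpha and stable retest scores. In either case these checks use survey data, after the items have been put to farmers.

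**Illustration of what farmer places would buy.** The documents give no misreading rate, so 20% and 30% are assumptions. If each of n debriefed farmers independently misreads an item with probability p, and every misreading is noticed, the chance of at least one signal is 1 − (1 − p)^n.

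| Assumed p | n = 0 | n = 5 | n = 10 |
|---|---|---|---|
| 0.30 | 0 | 1 − 0.7^5 = 0.83 | 1 − 0.7^10 = 0.97 |
| 0.20 | 0 | 1 − 0.8^5 = 0.67 | 1 − 0.8^10 = 0.89 |

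The n = 0 column only restates that no farmer is debriefed; it gives no credit for what professionals or the member check might notice. The other columns are upper limits, because detection will not be perfect.

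**The case against.** The best case for the plan is that farmers are not absent from the making of the questionnaire. Its items start from the words of interviewed farmers and relatives, and the form itself defines the diet. The member check is placed inside questionnaire development, just before the final version. Since member checking of the qualitative data is already covered in the Qualitative Data Analysis Plan, this second mention can be read as returning draft items to participants. The later validation also goes well beyond Cronbach alpha, and blood pressure is the trial's main outcome.

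Much of this stands, and it limits the point. A reader might infer that staff help is the only safeguard, that farmers certainly first meet the items in the survey, or that the planned checks could not reveal misreading. The documents do not support any of these: other safeguards are stated, the member check is ambiguous, and factor analysis, the yes/no comparison and retest could catch some forms of misreading. Nor should the detection percentages be read as properties of this trial.

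The objection does not supply a described test of comprehension. Quotations chosen and turned into items by investigators, guided by a theoretical model and sorted by experts, may no longer read as farmers would say them. Staff help comes too late to serve as a pretest, and a helper's explanation may shape the answer.

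**Conclusion.** The point holds in a limited form. The step called cognitive debriefing has 10 of 10 places filled by professionals. It can support content relevance, but it cannot observe farmers' understanding of the drafted items or the response scale. No other step is described as doing so before activity 2, although the member check might if it were specified.

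The effect is confined to the survey's acceptability level, its association with education, and the acceptability outcome named in the Activity 3 overview. It does not reach systolic and diastolic blood pressure, which are the main outcomes under Outcome Measures and the only ones modelled in the trial's Data Analysis Plan. The count of zero farmers needs no assumption. How much bias results cannot be derived from the documents. The 67% to 83% for five farmers rests on assumed misreading rates, independence and perfect detection.

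**What to change.** In Validation and Reliability, label the professionals' step as expert content review and give about five of the ten places to farmers who meet the survey's own criteria (Activity 2, Participants). Include some with no formal or only elementary schooling. Debrief them on the drafted items and the 4-point scale in Bahasa Indonesia, and revise the items before activity 2 starts.

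These farmers should preferably not have been interviewed in phase I. Phase I participants must already be using fruit and vegetables to control their blood pressure, a condition the survey does not impose. They will also have discussed the diet and supplied the wording, so they are among the farmers least likely to misread it.

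Alternatively, state in the Activity 1 overview that the member check tests the drafted items and scale with such farmers.

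The cost is a few short interviews and, if the total stays at ten, about half as many professional opinions on content. Adding farmers on top of the ten would avoid that loss at the price of a slightly larger exercise.
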